## 2. Final study protocol and statistical analysis plan

### 2.1 Trial design

This was a prospective double-blind randomized crossover study designed to compare the acute effect of unilateral STN and GPi stimulation on motor symptoms in several patients with PD. Participants with advanced PD who had previously undergone combined unilateral STN and contralateral GPi DBS were screened based on the inclusion and exclusion criteria. Following recruitment, participants were comprehensively evaluated under four randomized, double-blind conditions: (1) Med−STN+GPi−, (2) Med−STN−GPi+, (3) Med+STN+GPi−, and (4) Med+STN−GPi+. The symbol + means on, while − means off. The **intervention** section explains the details of these conditions. All participants and trained assessors were blinded to the conditions, and patients were randomly assessed over the course of two continuous days. (**Figure. 1**)

[figure not shown]

Figure. 1 Trial design.

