### 2.2 Patients

Participants were recruited from the Department of Functional Neurosurgery at Ruijin Hospital, Shanghai Jiao Tong University School of Medicine (Shanghai, China). A total of 10 patients with PD underwent combined unilateral STN and contralateral GPi DBS from September 2017 to September 2018. Following recruitment in April 2020 and screening, eight patients who had received the surgery for 2 to 3 years were included in this study. The inclusion criteria were: 1) diagnosis of idiopathic PD; 2) age between 55 and 75 years, both male and female; 3) treatment with combined unilateral STN and contralateral GPi DBS for 2 to 3 years and with optimal parameters for 3 months; and 4) a Hoehn-Yahr (H-Y) stage of less than 4 in the medication-off state. The exclusion criteria were: 1) history of serious psychosis; 2) history of intractable epilepsy (i.e., seizures); 3) diagnosis of severe cardiac, liver or kidney diseases, or other serious health conditions; 4) dementia (A Mini-Mental State Examination score of <24), inability to comprehend the experimental protocol or voluntarily provide informed consent; 5) lack of cooperation; 6) poorly controlled depression or anxiety. The patients in this study overlapped partly with those in our previous study published in 2020;^5^ those were, patients, 3, 7 and 8. Additionally, according to the asymmetry index, patients were divided into a symmetric group (asymmetry index <0.15, both Med− and Med+ conditions before surgery) and an asymmetric group (asymmetry index ≥0.15, either Med− or Med+ conditions before surgery), and the corresponding subgroup analysis was performed. The asymmetry index was a left-extremity to right-extremity ratio in the MDS UPDRS-III, which was calculated using the formula (left extremity – right extremity) / (left extremity + right extremity). A team of experienced multidisciplinary DBS specialists made the clinical decision regarding the specific DBS target to be used in each patient. That was, unilateral STN DBS was applied to treat the more severe side since we hypothesized that STN is more effective than GPi.

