#### 2.3.3 Concomitant interventions

Participants were asked to stop taking antiparkinsonian drugs for 12 h to stay in the Med− state until they completed the first set of assessments. Regular medication was taken one hour before the second set of assessments to maintain a Med+ state. All processes were repeated for the contralateral target on the next day.

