### 2.4 Randomization and blinding

The testing sequence of the treatment conditions was randomly assigned in a counterbalanced manner on the scheduled days. The order of the DBS conditions was determined by the clinician who randomly picked up one of the eight folded sheets with different conditions written on them (half of the first day GPi; half of the first day STN) but was not allowed to participate in any rating or evaluation. Throughout the study, all participants, raters, and statisticians were blinded to treatment conditions. A movement disorder specialist was responsible for programming. In addition, motor symptom evaluation in this experiment was performed by an experimenter who was blinded to the study protocol and did not participate in data analysis or interpretation. Two raters who were blinded to the conditions conducted the video assessments independently, after which the average rating scores were calculated. For subscores with large deviancy, the final scores were determined after re-evaluation.

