### 2.6 Data analysis

There were two types of comparisons conducted in this study. The first was the comparison between unilateral STN+ and GPi+ within the same patient group in Med− and Med+ conditions, and the second was the comparison between asymmetric and symmetric groups for the different patient groups in the same condition. Before the comparisons, the Shapiro-Wilk test was used to test the normality of data in each group, yielding the W statistic and *P*-value reflecting the evaluation criteria of distribution. For normally distributed data, a parametric test of the Student’s t-test was used to assess the difference between groups. For the non-normally distributed data, the non-parametric Wilcoxon test was applied to compare the differences. The first comparison mentioned was based on the paired Student’s t-test and Wilcoxon signed-rank test. The second comparison was based on the independent Student’s t-test and Wilcoxon rank-sum test. All three tests mentioned were two-tailed tests with a *P*-value*<0.05* reflective of statistical significance. Statistical calculations and techniques were performed using R-4.0.2.

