## 3. Summary of changes and reasons

| **Original study protocol and statistical analysis plan** | **Changes** | **Reasons** |
| --- | --- | --- |
| We originally intended to enroll a total of 10 patients with a left-extremity to right-extremity ratio of less than 0.15 on the MDS UPDRS-III in the both Med on and Med off states. | We modified the previous requirement of an asymmetry index less than 0.15 in the inclusion criteria.  8 patients were eventually enrolled, only half of whom met the asymmetry index of less than 0.15. | DBS treatment with asymmetric targets was firstly used mainly in patients with asymmetric motor symptoms in both limbs in the pilot study. A total of 10 patients met the requirement of a 2- to 3-year follow-up period, but only 8 patients could be included based on the inclusion criteria and patient preference. |
| We originally intended to perform stimulation parameter adjustments prior to assessments. | In practice, we kept the optimal parameters and did not adjust them before the assessment. | Retaining the stable optimal parameters allows a better comparison of the two targets in daily treatment. |
| We originally intended to perform the assessment in the Med on condition 45 minutes after taking the parkinsonism drugs. | In practice, the assessment in Med on condition was performed 1 hour after taking the medication. | Previous evidence suggests that 1 hour may be more reasonable and that the patient is in a better state. |
| The Wilcoxon matched-pairs signed-rank test and χ2 test were considered to be used. | the Shapiro-Wilk test was used to test the normality of data in each group, yielding the W statistic and *P*-value reflecting the evaluation criteria of distribution. For normally distributed data, a parametric test of the Student’s t-test was used to assess the difference between groups. For the non-normally distributed data, the non-parametric Wilcoxon test was applied to compare the differences. | The final statistical analysis is more standardized. |

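### The two-day crossover is analysed without a day term, which can cost power in the full sample and, if test order is uneven within a subgroup, can shift the subgroup results

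*Supplement*

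**What the plan says.** All references are to the final plan (Supplement, part 2), apart from one line in part 3.

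- **Design.** Section 2.1: "This was a prospective double-blind randomized crossover study". Each target has its own day. Section 2.3.3 adds: "All processes were repeated for the contralateral target on the next day".
- **Order.** Section 2.4: "The testing sequence of the treatment conditions was randomly assigned in a counterbalanced manner on the scheduled days". A clinician "randomly picked up one of the eight folded sheets with different conditions written on them", and the sheets were divided as "half of the first day GPi; half of the first day STN".
- **Patients and subgroups.** Section 2.2: "eight patients who had received the surgery for 2 to 3 years were included in this study". The same section divides them by a pre-surgical asymmetry index and announces a subgroup analysis. Part 3 gives the sizes: "8 patients were eventually enrolled, only half of whom met the asymmetry index of less than 0.15". That makes four symmetric and four asymmetric patients.
- **Analysis.** Section 2.6 tests normality and then chooses between a parametric and a rank test. For STN against GPi: "The first comparison mentioned was based on the paired Student’s t-test and Wilcoxon signed-rank test". The symmetric and asymmetric groups are compared with the independent-sample counterparts.

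No day, period or sequence term appears in section 2.6, nor any check for one. Nothing says that test order was balanced within the asymmetry groups. The final plan states no power, SD or expected difference.

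**The concern.** The design controls for day, but the analysis does not use that control. On day 2 the same patients repeat the same assessments after a further overnight drug withdrawal. Practice, fatigue or the second withdrawal could therefore move scores up or down. A plain paired test pools both orders, so any such shift appears as extra scatter between patients tested STN-first and those tested GPi-first. With eight patients that scatter could hide a real difference between targets.

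The subgroups raise a separate question. A draw balanced over eight patients need not be balanced within each four. Where it is not, part of the day effect stays in the subgroup's STN-GPi difference.

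**Working it through.** The plan has no figure of its own to reproduce.

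**Inputs from the documents.** n = 8 (section 2.2); two orders, half and half (2.4); subgroups of 4 and 4 (2.2 and part 3); two-sided 0.05 (2.6).

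**Assumed.** The eight sheets were drawn without replacement, giving 4:4. The counterbalancing in section 2.4 supports this but does not spell it out. The day effect π (day 2 minus day 1) ranges from 0 to 1.5 and the true target effect τ is 0, 1.0 or 1.2, both in SDs of the paired difference.

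**Model.** For each patient d = STN - GPi = τ + π·s + e, where s = +1 for GPi-first, s = -1 for STN-first, and e has SD 1.

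1. *Bias, full sample.* The mean of s is (4 - 4)/8 = 0, so the mean of d is τ whatever π is.

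2. *Residual, full sample.* The sample variance of s is 8/7, so the expected variance of d is 1 + (8/7)π². That is 1.07, 1.29, 2.14 and 3.57 at π = 0.25, 0.5, 1.0 and 1.5.

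3. *Day-adjusted estimate.* Take the average of the two sequence means, with the error pooled within sequence on 4 + 4 - 2 = 6 df. Its standard error is (s_w/2)·√(1/4 + 1/4) = s_w/√8, where s_w is the within-sequence SD and is free of π. The plain paired t-test has 7 df.

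4. *Rejection rates.* 200,000 simulated trials per setting, normal errors, t-tests only (the signed-rank test was not simulated):

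| π (SD) | Type I error, plain | Power plain/adjusted, τ = 1.0 | Power plain/adjusted, τ = 1.2 |
|---|---|---|---|
| 0 | 5.1% | 68% / 66% | 83% / 81% |
| 0.25 | 4.4% | 66% / 66% | 81% / 81% |
| 0.5 | 3.0% | 58% / 66% | 75% / 81% |
| 1.0 | 0.7% | 34% / 66% | 51% / 81% |
| 1.5 | 0.06% | 11% / 66% | 22% / 81% |

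 The adjusted test holds about 5% type I error throughout. Adjustment costs about 2 points when π = 0, breaks even near 0.25 SD and gains beyond that.

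5. *Order split within a subgroup of four.* P(k GPi-first) = C(4,k)·C(4,4-k)/C(8,4), with C(8,4) = 70. So 2:2 has probability 36/70 = 51.4%, 3:1 either way 32/70 = 45.7%, and 4:0 either way 2/70 = 2.9%. The chance of an uneven split is 34/70 = 48.6%.

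6. *Displacement.* It equals π times the subgroup mean of s: 0 at 2:2, ±(3 - 1)/4 = ±0.5π at 3:1, and ±π at 4:0. Because the total is 4:4, the other subgroup has the mirror-image split. The two STN-GPi differences therefore move in opposite directions, and the gap between them shifts by π at 3:1. Averaged over all possible draws, the displacement is zero.

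7. *Subgroup type I error, plain paired t-test, π = 1.0.* 1.0% at 2:2, 3.7% at 3:1, 28.7% at 4:0, and 3.0% over all draws.

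8. *Day adjustment within a subgroup of four.* The test has 4 - 2 = 2 df. At an assumed τ = 1.5 SD and π = 0, power falls from 53% to 39% (2:2) or 32% (3:1). At 4:0 it cannot be computed. Re-randomising order within the subgroup does not help: there are C(4,2) = 6 arrangements at 2:2 and 4 at 3:1, so p cannot fall below 1/6 or 1/4.

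**The case against.** The strongest reply is that the plan's main test remains valid. Counterbalancing removes the day effect from the full-sample estimate, and the plain paired test errs on the cautious side. A reader might infer from the missing day term that the main result is biased or prone to false positives. Steps 1 and 4 show the opposite for a 4:4 draw.

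The reply also says the power loss is hypothetical. The two days follow the same procedure, and two raters blinded to condition score the videos. Nothing in the documents shows a day effect above 0.25 SD, and with none the plain test is slightly better. The fall from 83% to 51% needs a day effect as large as the whole SD of the paired differences. This stands as a limit on the size of the claim. It does not justify leaving day out, because the price is about 2 points and the possible gain is much larger.

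On the subgroups, a reader might infer that their results are biased. The documents do not support that either. It takes both a day effect and an uneven split; the realised split is not given, 51% of draws are even, and the average displacement is zero. The reply is also right that a day-adjusted test on four patients is no remedy (step 8).

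**Conclusion.** The point holds in a limited form. The final plan randomises a two-day crossover with counterbalanced order and then analyses it as if day did not exist. In the full sample the consequence is possible loss of power. It is nil or slightly in the plan's favour for day effects up to about 0.25 SD, 6 to 8 points at 0.5 SD (81 - 75 and 66 - 58), and 30 to 32 points at 1.0 SD (81 - 51 and 66 - 34). A non-significant comparison of targets could partly reflect this.

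In each subgroup of four, a day effect can displace the STN-GPi difference by half its size (46% chance) or all of it (3%), with opposite signs in the two subgroups. It could then pass for a dependence of the target effect on asymmetry.

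All magnitudes rest on assumed values of the day effect and target effect, normal errors and the t-test. The absence of full-sample bias rests on the draw having given 4:4. The allocation probabilities rest on that and on order being drawn without regard to asymmetry group.

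**What to change.** **All eight patients.** In each medication state, analyse STN against GPi by randomised sequence: average the two sequence means of the STN-GPi difference and take the error within sequence (6 df). Alternatively, fit a mixed model with target and day as fixed effects and patient as random. Report the estimated day effect and the number of patients in each order.

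**Symmetric and asymmetric subgroups.** Report how many patients in each were tested STN-first and GPi-first, and present the STN-GPi results as descriptive. Do not run a day-adjusted test on four patients.

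**Cost.** New wording in section 2.6 and a re-run on data already collected. The full-sample analysis gives up 1 df, about 2 points of power if there is no day effect. Drawing order separately by asymmetry group is not an option here, because the final plan describes assessments already carried out.

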### 2.5 Trial outcomes

Acute turning-on effects of unilateral STN stimulation versus unilateral GPi stimulation on motor symptoms in each patient were compared as the primary outcome. Motor symptoms were defined by the MDS UPDRS-III scores which ranged from 0 to 132, with higher scores indicating more severe motor symptoms. To gain insight into the specific effects of each target, we classified the MDS UPDRS-III subscales into three categories: 1) axial signs, as measured by scores on speech, facial expression, arising from a chair, posture, gait, freezing of gait, and posture stability; scores could range from 0 (no axial signs) to 28 (severe axial signs); 2) STN-stimulated contralateral limb symptoms; and 3) GPi-stimulated contralateral limb symptoms. Limb symptom severity was measured using the subscale scores of the corresponding limb on rigidity, finger tapping, hand movements, hand pronation supination, toe-tapping, leg agility, posture tremor, kinetic tremor, and resting tremor amplitude; scores could range from 0 (no limb symptoms) to 52 (severe limb symptoms). The Berg Balance Scale (BBS) was also compared as a second outcome at the 2- to 3-year follow-up. The patient’s daily dose of antiparkinsonian medication was converted into a levodopa equivalent daily dose (LEDD).

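### The single primary outcome is tested in two medication states at P<0.05 each, with neither state decisive and no adjustment, so its false-positive rate is about 7–10% rather than 5%

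*Supplement*

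**What the plan says.** All references are to Part 2 of the Supplement, the final protocol and analysis plan, unless stated otherwise.

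- **Primary outcome (Section 2.5).** "Acute turning-on effects of unilateral STN stimulation versus unilateral GPi stimulation on motor symptoms in each patient were compared as the primary outcome". Motor symptoms are the MDS UPDRS-III score on its 0 to 132 range, which is the total. No medication state is named.
- **How it is tested (Section 2.6).** "The first was the comparison between unilateral STN+ and GPi+ within the same patient group in Med− and Med+ conditions". The primary comparison is thus made twice.
- **Threshold (Section 2.6).** "All three tests mentioned were two-tailed tests with a" P-value below 0.05 "reflective of statistical significance". The same level serves every comparison.
- **Other outcomes (Section 2.5).** For the subscores, "we classified the MDS UPDRS-III subscales into three categories": axial signs and the limbs opposite each stimulated target. The Berg Balance Scale (BBS) "was also compared as a second outcome at the 2- to 3-year follow-up".
- **Groups (Sections 2.2 and 2.6).** Patients are split by asymmetry index, "and the corresponding subgroup analysis was performed". Section 2.6 adds a comparison of the two groups within the same condition. Section 2.1 lists four conditions.

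The final plan gives no testing order, no multiplicity adjustment and no rule for reading the two medication states together. It does not call any of these analyses exploratory.

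**The concern.** One primary outcome tested twice gives two chances to find a difference between the targets. Because the plan does not say which state decides, or whether both must agree, a result in only one state could be presented as the primary finding. Section 2.2 also records a prior hypothesis that STN is the more effective target, so a single favourable state would be easy to read as confirmation. With eight patients, a chance result in one state is a real possibility.

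The remaining analyses make this worse in a lesser way. They use the same threshold and carry no label that would tell a reader to weigh a P-value below 0.05 differently from one on the primary outcome.

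**Working it through.** **Inputs**

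| Quantity | Value | Source |
| --- | --- | --- |
| Level of each test | two-sided 0.05 | Section 2.6 |
| Medication states for the primary comparison | 2 | Section 2.6 |
| Outcomes | 5 (total score, 3 subscores, BBS) | Section 2.5 |
| Conditions | 4 | Section 2.1 |
| Patients | 8, of whom 4 symmetric and 4 asymmetric | Section 2.2; Part 3, summary of changes |

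The final plan states no family-wise level, power or number of tests, so it offers no figure of its own to reproduce.

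**Step 1. The two primary tests.** The chance of at least one false positive when neither state has a true difference:

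- Independent tests of exact size 5%: 1 − 0.95² = 0.0975, or 9.75%.
- Correlated paired t-tests, n = 8, simulated with 200,000 runs per value: about 9.1% at correlation 0.5, 8.5% at 0.7 and 7.3% at 0.9.
- Two exact signed-rank tests, n = 8: the attainable P-values are 0.0078, 0.0156, 0.0234, 0.0391, 0.0547 and upwards. The largest below 0.05 is 10/256 = 0.0391, so each test has true size 3.9%. If independent, 1 − (1 − 0.0391)² = 0.077, or 7.7%. Positive correlation lowers this; with perfect dependence it would be 3.9%.

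The documents give no correlation between the two states, so the values above are assumptions spanning a range.

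**Step 2. The number of further tests.** The documents give no count, so two readings are set out.

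- Within-patient tests in the whole cohort only: 5 outcomes × 2 states = 10. Between-group tests: 5 outcomes × 4 conditions = 20. Total 30, less the 2 primary tests = 28.
- Within-patient tests in all patients and in each subgroup: 5 × 2 × 3 = 30. With the 20 between-group tests, total 50, less 2 = 48.

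**Step 3. Whether an adjustment is workable with eight patients.**

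- Splitting the level, 0.025 to each primary test, gives 1 − 0.975² = 0.0494 if independent, and at most 5% under any dependence. Holm's procedure has the same bound.
- The smallest two-sided signed-rank P at n = 8 is 2/256 = 0.0078. This is below 0.025, so Holm's first step can be met even if the rank test is used.

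**The case against.** The best defence is that 0.05 is a per-test threshold and that the plan nowhere promises a family-wise 5%. That is correct: the plan makes no false statement about its error rate. What it lacks is control over one outcome that it calls primary and tests twice. A related defence is that Med− and Med+ are separate questions, each entitled to its own 5%. The plan could have said so, but it names one primary outcome. Nor does it say that one state alone establishes superiority; the difficulty is that it says nothing either way.

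Some hierarchy does exist. Section 2.5 separates the primary outcome from a second one and introduces the subscores as a means of understanding what each target does. The lack of order therefore bears chiefly on the two medication states.

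A reader might also infer that a full set of 50 tests yields 2.5 chance findings, or that the ten whole-cohort paired tests carry a 40% chance of at least one. The documents do not support either as a firm figure:

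- Fifty is the larger of two readings of the subgroup analysis.
- The figure of 2.5 (50 × 0.05) needs every test to attain 5% and every null to be true. A signed-rank test in four patients cannot go below P = 0.125, and a rank-sum test of four against four attains only 2/70 = 0.029. If all tests were exact rank tests, the expected number would be 10 × 0.039 + 20 × 0 + 20 × 0.029, about 1.0. The plan mixes t and rank tests, so even with every null true the figure lies between about 1.0 and 2.5.
- The 40% (1 − 0.95¹⁰) assumes independence among overlapping scores from the same eight patients. It also treats the limb subscores as true nulls, although each compares a stimulated side with an unstimulated one, so a difference is expected by design. They make up 4 of those 10 tests; the other 6 give 1 − 0.95⁶ = 26.5%, still assuming independence.

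Finally, the word exploratory stood in the sample-size section of the original plan (Section 1.8.1). Its absence from the final plan is not a fault in itself. It matters only because the current text cannot be defended by a label that it does not contain.

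**Conclusion.** The point holds for the primary outcome. Two tests at 0.05, with no decisive state and no adjustment, give about a 7–10% chance of at least one false-positive primary result instead of 5%. The range covers paired t-tests from independence to a correlation of 0.9, and independent exact signed-rank tests. It takes each t-test to have its nominal size and does not model the choice between tests by the Shapiro-Wilk result. Strongly correlated signed-rank tests would fall below the range.

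For the rest, the finding is limited to this: about 28 to 48 further tests share the threshold, and the final plan does not label them exploratory. No single overall error rate for the whole set can be drawn from the documents.

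This is a gap in error control that should be closed. It does not invalidate the trial.

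**What to change.** In Section 2.6:

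1. Apply Holm across the Med− and Med+ tests of the total MDS UPDRS-III. Compare the smaller P-value with 0.025; only if it is significant, compare the other with 0.05.
2. Report the subscores, the BBS, the subgroup results and the between-group results as estimates with 95% confidence intervals, labelled exploratory and without claims of significance.

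Holm treats the two states alike. Naming one state as decisive, or fixing a sequence, would also hold 5% if settled beforehand. However, the final plan is written in the past tense, after enrolment, so a choice made now could not be shown to be independent of the data and would not restore error control.

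The change is to wording only, with no new patients or measurements. The price is slightly less power for each primary test, and secondary results can no longer be called significant.
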